### Statistical analyses

All analyses follow an a priori analytic plan. The primary outcomes are health behaviour and preventative care use, as listed in Table 2[2,5,21-25]. Secondary outcomes include mortality, need for long-term care (living in nursing home, or designated as requiring long-term care according to the German long-term care insurance system), and self-reported information on health status (vision, hearing, self-perceived health status, pain, depressive symptoms, falls history, and functional status).

To conduct planned sensitivity and subgroup analyses of primary outcomes, two composite scores will be created: one for adherence to positive health behaviour, and one for use of recommended preventative care. The percentage of health behaviour domains (Table 2) for which the patient showed a positive level of performance, and the percentage of recommended preventative care measures (Table 2) the patient had used will be determined. We will impute composite scores for individuals in whom ≤ 20% of the required outcome data were missing. Imputation will be conducted as follows: based on available baseline variables multiple linear regression models (using the complete base-line information and household status) will be derived in the subset of persons with complete data on outcomes, and subsequently, these models will be used to impute composite score estimates in persons with missing information.

Outcome analyses of the randomised controlled study will be conducted for each site separately in keeping with the inter-site variations of reinforcement methods. The main analyses will compare primary and secondary outcomes between intervention and control groups at follow-up. In these analyses, the fact that participants living in the same household were allocated to the same group will be taken into account by adding the information on household membership to generalised estimating equations (GEE) models [26,27]. Subgroup analyses will be used to evaluate whether the intervention effects differ between predefined subgroups of the population. Firstly, outcomes will be compared between older persons at high risk (Pra > 0.28) and those at low risk (Pra ≤ 0.28) for hospital use [10,11], based on the hypothesis that this type of intervention might have greater positive effects in persons at low risk [28]. Second, for the randomised study in Hamburg and Solothurn, an additional analysis will be carried out to evaluate the independent effects of the site-specific reinforcement on primary outcomes: multivariate regression analyses will be conducted using the composite scores as outcome variables, and participation status in the reinforcement as an independent variable, controlling for intervention allocation status and available participant base-line characteristics. Finally, sensitivity analyses will be conducted to evaluate for potential bias resulting from missing outcome data. First, all analyses will be repeated by adjusting GEE models for base-line age, gender, self-perceived health and number of physician visits reported. Second, primary outcome analyses will be repeated by using with composite scores of health behaviour and use of preventative care which will be derived from imputed outcome estimates in persons with partially missing information.

We will also evaluate changes in preventative care use, health behaviour, and health status between baseline and the one-year follow-up among persons in the intervention group. This analysis will be possible because persons in the intervention group received the HRA-O questionnaire both at base-line and at one-year follow-up. This analysis will adjust for household membership and base-line variables (age, gender, self-perceived health status, health care use prior to base-line). These pre-post analyses will be restricted to the intervention group since primary outcomes were not measured in the control group at baseline.

Outcome analysis of data from the concurrent comparison group will include a comparison of primary and secondary outcomes between the intervention group and the concurrent comparison group. The primary analysis will be a comparison of primary outcomes adjusted for base-line factors.

Categorical and binary outcome data will be analysed using chi-square tests; continuous outcome data will be compared using t-tests if normally distributed, Mann-Whitney U test if skewed. Number of physician visits will be analysed with ordered logistic regression models. To allow for within-household clustering, Generalised Estimating Equations (GEE), assuming an exchangeable correlation structure, will be used to analyse all outcomes [27]. Data will be analysed using the SAS programme [29].

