### Recruitment of older persons

Participating GPs recruited older persons to the project in four steps (Figure 1). Firstly, all practices generated lists of their older patients. The age cut-off for listing patients was based on the country-specific age used for planning and delivery of services to the elderly. In London and Solothurn, an age cut-off of 65 years was selected, in Hamburg a cut-off of 60 years. In a second step, practices were asked to exclude patients meeting the following exclusion criteria: needing human assistance for performing basic activities of daily living or living in a nursing/residential home (in Germany, nursing care according to the German long-term care insurance system); cognitive impairment (i.e. possible dementia, equivalent to a Mini Mental Status score of 24 or less [9]; terminal disease; and/or inability to speak the regional language. In a third step, GPs sent an invitation letter to all individuals remaining on the list. The invitation included an information sheet describing the planned project, the Pra (Probability of repeated admissions) questionnaire [10,11], and a self-administered question on self-perceived need for human help in basic activities of daily living [12]. Patients were asked to return the completed questionnaire if they were interested in participating in the study, and to give informed consent according to the policies of the responsible institution. In London and Solothurn patients were asked to complete and return a written consent form. In Hamburg patients were informed that by returning the questionnaire they agreed to participate in the study. All patients were informed that they could withdraw from the project without negative impact on their care. In a fourth step, persons reporting a need for human assistance in performing basic activities of daily living in the questionnaire, those returning an incomplete Pra questionnaire, and those declining participation (by not returning the brief questionnaire or by returning the questionnaire with an explicit statement of refusal) were excluded from the study. The remaining persons were included in the final list of participants in the study.

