### Data collection

Prior to randomisation, participant age and gender were recorded from practice registers. Information on base-line self-perceived health status, prior health care use, and instrumental support were derived from the Pra questionnaire [10]. In addition, for the participants in London, the Townsend score [19], a measure of social deprivation based on indicators of the older person's living location, was derived from the participants' address information.

At the one-year follow-up, surviving participants of all groups (intervention, control, and concurrent comparison group) were sent a HRA-O questionnaire with additional questions on health care use [10] and on patient self-efficacy [20]. This follow-up questionnaire included all items required for outcome analysis, as listed in Table 2. In addition, the one-year follow-up questionnaire was used for obtaining information on socioeconomic information and self-reported chronic conditions among participants in the control and concurrent comparison groups. No reminders were sent to persons not returning this questionnaire. To reduce the amount of missing information on preventative care in the London sample, practices were asked to review patient medical records for information on preventative care use (vaccination coverage, blood glucose and cholesterol measurement, colon cancer screening) for patients who had returned the 1-year follow-up questionnaire but had incomplete information on some items of preventative care (n = 44 intervention group, n = 33 control group, n = 20 concurrent comparison group).

**Table 2 T2:** List of primary outcomes used in the PRO-AGE study at the follow-up: health behaviour and preventative care use

**Domain**	**One-year outcome analysis (all sites)**	**Two-year outcome analysis (Solothurn only)**

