### Sample size/power calculation

We calculated the required sample size for detecting, at a two-sided significance level of 0.05 and with a power of 80%, a postulated 30% difference in positive health risk behaviour or preventative care use in the intervention group as compared to controls at the one-year follow-up. For this calculation, a prevalence of positive behaviour or preventative care use among controls of 20% was assumed, based on pilot data in a comparable sample of community-dwelling older persons [6]. Based on a 1:1 randomisation ratio and a predicted drop-out rate at one year of 20%, the required sample size was 1000 persons per group. In Hamburg and Solothurn, due to limitations in resources available for offering the intervention (group sessions, home visits), a randomisation rate of 1:2 was preferable. Based on a 1:2 randomisation rate, and on the same drop out rate, the required sample size was 763 persons in the intervention group and 1525 persons in the control group.

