### Comparison between groups of participants

Table 4 describes the available base-line characteristics of the study participants according to study sites and group allocation. This is to evaluate the success of randomisation. Within each site, prevalence rates were similar between intervention and control groups. In contrast, there were some relatively minor, but statistically significant differences between persons of the concurrent comparison group and persons of the intervention group (Table 4). Information on education, living alone status, and chronic conditions was derived from baseline HRA-O questionnaire (intervention groups: administered at the start of the project after randomisation; control and concurrent comparison groups: administered at the one-year follow-up). Missing values are due to non-response (all groups) or attrition (death, move away, and move to nursing home) in the control and concurrent comparison groups.

**Table 4 T4:** Self-reported baseline characteristics of the PRO-AGE study participants, according to site and group assignment

**Baseline characteristics**	**London (U.K.)**			**Hamburg (Germany)**			**Solothurn (Switzerland)**		
	**Intervention group**	**Control group**	**Concurrent comparison group**	**Intervention group**	**Control group**	**Concurrent comparison group**	**Intervention group**	**Control group**	**Concurrent comparison group**

Age (years)	74.7 ± 6.4 (1240)	74.4 ± 6.2 (1263)	74.9 ± 6.5 (636)	71.9 ± 7.7 (878)	71.8 ± 7.6 (1702)	72.0 ± 8.2 (746)	74.5 ± 5.8 (874)	74.5 ± 6.1 (1410)	74.2 ± 6.0 (1171)
Female gender	55.3% (686/1240)	54.6% (689/1263)	57.5% (366/636)	61.5% (540/878)	63.3% (1077/1702)	68.2%* (509/746)	56.9% (497/874)	56.5% (796/1410)	57.0% (667/1171)
Fair/poor self-perceived health	24.5% (304/1240)	27.2% (343/1263)	27.4% (174/636)	38.6% (339/878)	38.5 (656/1702)	39.5% (295/746)	19.9% (174/874)	24.8% (349/1410)	23.6% (276/1171)
≥1 hospital admission over past 12 months	14.0% (173/1240)	14.6%) (185/1263)	14.2% (90/636)	21.2% (186/878)	21.2% (360/1702)	22.5% (168/746)	19.9% (174/874)	18.5% (261/1410)	17.7% (207/1171)
> 6 doctor visits over past 12 months	19.0% (236/1240)	24.3% (307/1263)	23.4% (149/636)	49.9% (438/878)	49.9% (849/1702)	44.0%* (328/746)	24.0% (210/874)	24.3% (343/1410)	28.7%* (336/1171)
No available caregiver if needed	17.6% (218/1240)	14.8% (187/1263)	19.2% (122/636)	17.8% (156/878)	18.9% (322/1702)	20.0% (149/746)	9.8% (86/874)	11.6% (163/1410)	8.8% (103/1171)

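### One-year functional status has no value for participants known to be in long-term care who do not return the form, and no planned check restores them to that comparison

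*Protocol article*

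**What the plan says.** All references are to the protocol article.

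- **Outcome.** Statistical analyses lists mortality, need for long-term care and "self-reported information on health status (vision, hearing, self-perceived health status, pain, depressive symptoms, falls history, and functional status" as secondary outcomes. These are compared between intervention and control in the main analyses.
- **One-year source.** Data collection states that "surviving participants of all groups (intervention, control, and concurrent comparison group) were sent a HRA-O questionnaire", and that people who did not return it got no reminder.
- **What is known about non-responders.** The same section obtains survival and permanent long-term care for non-responders from GPs and, where available, registers. Long-term care means living in a nursing home in London and Solothurn. In Hamburg it means requiring nursing care under the German insurance system.
- **Entry rule.** Recruitment of older persons has one exclusion for "needing human assistance for performing basic activities of daily living or living in a nursing/residential home".
- **Missing values.** Comparison between groups of participants explains gaps in some Table 4 items by non-response in all groups or by "attrition (death, move away, and move to nursing home) in the control and concurrent comparison groups".
- **Missing-data checks.** Statistical analyses names two. One repeats all analyses with GEE models adjusted for four baseline variables. The other imputes the primary composite scores when at most 20% of the required outcome data are missing.
- **Two years, Solothurn only.** Need for help in basic activities was asked again, and non-responders were telephoned or visited by a blinded assistant.

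**The concern.** Moving into care happens after randomisation and is closely tied to function. A one-year comparison restricted to people who return a self-report form is partly conditioned on that event. The trial holds the information that would fill the gap for these people, and its own entry rule treats nursing-home residence and dependence in basic activities alike. In Hamburg the follow-up definition of long-term care is itself a statement about needing care. The article nevertheless gives this information no role in the functional outcome.

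What is at stake is the direction of the functional result. Suppose the intervention kept frail people at home longer. They would remain in the functional comparison as dependent, while similar controls who moved and did not reply would drop out of it, so a benefit could look like harm. If the intervention sped up entry into care, the functional comparison could look too favourable.

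**Working it through.** **Stated figures.** The article gives no figure for functional status, long-term-care moves or dependence. Its only sample-size figures (1000 per group at 1:1; 763 and 1525 at 1:2) concern the primary outcomes. With 20% against 26%, two-sided 0.05, 80% power, continuity correction and 20% drop-out, they come out close: 805/0.8, rounded up to 1007; and 596/0.8 = 745 with 2 × 745 = 1490. The present point does not depend on them.

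**Step 1: who lacks a value.** All survivors are sent the form, so a mover who returns it is kept. A mover who does not return it has no self-report. Their long-term-care status is sought from GPs and registers, but no text turns it into a functional value.

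**Step 2: do the planned checks reach them?** Adjusting a GEE model for baseline covariates cannot bring back a person with no outcome. The imputation covers only the two primary composite scores, and only for people with at most 20% missing. Neither reaches this group.

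**Step 3: how much is missing at one year from all causes.** Controls first received the full questionnaire at one year, so the Table 4 denominators for living alone give an approximate figure:

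- London: 1263 − 1047 = 216; 216/1263 = 17.1%
- Hamburg: 1702 − 1349 = 353; 353/1702 = 20.7%
- Solothurn: 1410 − 976 = 434; 434/1410 = 30.8%

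The share due to long-term care is not given.

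**Step 4: effect on the level (assumed range).** Let L be the share of an arm that moved to long-term care and did not return the form, and d the dependence rate in everyone else. The responders-only analysis gives d. Counting movers as dependent gives L + (1 − L)d, so the understatement is L(1 − d).

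| d | L = 1% | L = 2% | L = 4% |
|---|---|---|---|
| 5% | 6.0% | 6.9% | 8.8% |
| 10% | 10.9% | 11.8% | 13.6% |

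The understatement runs from 0.01 × 0.90 = 0.9 points to 0.04 × 0.95 = 3.8 points.

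**Step 5: effect on the group difference.** With the same d in both arms, the responders-only difference is 0. The difference with movers counted is (L_intervention − L_control)(1 − d).

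- Equal L: 0.
- 1% against 2%: 0.01 × 0.95 = 0.95 points (d = 5%) or 0.01 × 0.90 = 0.90 points (d = 10%).
- 1% against 4%: 0.03 × 0.95 = 2.85 points or 0.03 × 0.90 = 2.70 points.

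The sign follows whichever arm has more non-returning movers.

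**Step 6: one scenario with no true effect (assumed).** Take 8% dependent in each arm, of whom 2.0% of controls and 1.5% of intervention participants are in care, with no mover replying. Responders-only gives 6.0/98.0 = 6.1% against 6.5/98.5 = 6.6%, a ratio of 1.08 instead of 1.00. With equal shares in care the ratio is 1.00.

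**The case against.** The strongest reply is that the trial does account for these people. Need for long-term care and mortality are named secondary outcomes, compared between arms, with status sought for non-responders. In the scenario of Step 6 the long-term-care outcome would show 1.5% against 2.0%, so a reader would see the compensating result. This stands. A reader might infer that people in care leave the trial's analysis, or that the worst outcomes are hidden; the article supports neither. What remains is that a separate outcome does not correct a functional comparison made among those who replied.

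Three other stronger readings also fail.

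- One might think the mailing to all survivors contradicts the listing of nursing-home moves as attrition. It does not: a person can be sent a form, move and not reply. The attrition remark also explains gaps in Table 4 and is not a rule for analysing secondary outcomes.
- One might suppose the loss grows by two years in Solothurn. No figure supports that, and non-responders there were actively contacted.
- One might take the ratio of 1.08 as an estimate. It comes entirely from an assumed difference in moves. With about 1000 per arm, its 0.5-point gap compares with a standard error of about 1.1 points.

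It can also be said that coding is left to the analysis plan, which is not shown, and that the trial was not powered for functional decline, as the Discussion admits. The second point stands and limits the weight of the finding. The first stands only in part. The article itself fixes the outcome as self-report and names its missing-data checks, and the Discussion says the plan takes the described limitations into account. For this group those checks do not.

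**Conclusion.** The point holds for one-year functional status only. Known movers into permanent long-term care who do not return the form have no value in that comparison, and neither planned check restores them. This follows from how the outcome and the checks are defined; the article does not state it as an exclusion rule.

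The size cannot be taken from the documents. If 1% to 4% of an arm are non-returning movers and 5% to 10% of the others are dependent, dependence is understated by 0.9 to 3.8 points. The group difference is biased only if moves or response differ by arm: by about 0.9 points at 1% against 2%, by 2.7 to 2.9 points at 1% against 4%, and not for this reason when the rates are equal. The calculation assumes that every known mover counts as dependent and that other non-response is unrelated to function. It concerns an unpowered secondary outcome, so this is a cheap improvement and not a threat to the main conclusions.

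**What to change.** For one-year need for help or functional dependence, add an analysis that counts every randomised person known to be in permanent long-term care at follow-up as dependent. Show it beside the responders-only result. Give a table by arm and site with four categories: independent at home, dependent or in care, dead, unknown. Read the result jointly with the long-term-care and mortality outcomes.

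The article sets no cut-off for dependence, and the questionnaire covers both basic and instrumental activities. The added analysis therefore needs a stated binary definition; where function is analysed as a score, the table carries the information.

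The cost is recoding data already collected from GPs and registers. The small downside is that the outcome then mixes self-report with GP- or register-reported status. Long-term care has a different definition in Hamburg than at the other two sites, but analyses are already planned by site.

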### Randomisation of participants

Participating patients of GPs who had received the training were randomly allocated to intervention and control groups by the independent study centre using a computer generated allocation sequence. People living in the same household were allocated to the same group. The ratio of allocation of participants to intervention and control groups was 1:1 in the London sample and 1:2 in the Hamburg sample. In the Solothurn sample, a 1:1 randomisation ratio was used in the initial study phase, and then changed to 1:2, resulting in an average ratio of 1:1.6. Variation in randomisation rates was related to budgetary constraints (see sample size calculation), which became apparent after the project was underway. Participants allocated to the intervention group were offered HRA-O with personal reinforcement. Those allocated to the control group received usual care.

Participants of GPs who had not received additional training formed the concurrent comparison group. All patients in this group continued to receive usual care during the study period. GPs in this group received only general project information during the study period, and were offered the training after the end of the project follow-up.

Final inclusion of study participants started in November 2000 and was completed in London in October 2001, in Hamburg in September 2001, and in Solothurn in February 2002.

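### Solothurn changed its allocation ratio from 1:1 to 1:2 part-way, but the randomised analyses model household only, so any outcome difference between the two phases biases the comparison

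*Protocol article*

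**What the plan says.** The Statistical analyses section of the protocol article analyses each site separately and compares the arms by "adding the information on household membership to generalised estimating equations (GEE) models". It later applies exchangeable-correlation GEE, for within-household clustering, to every outcome. The one covariate-adjusted repeat of these analyses is a sensitivity analysis: "adjusting GEE models for base-line age, gender, self-perceived health and number of physician visits reported". The extra regression on taking up the reinforcement in Hamburg and Solothurn adjusts for available baseline characteristics, but it answers a different question, and the baseline table lists neither GP nor phase.

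Under Randomisation of participants, London is described as 1:1 and Hamburg as 1:2. For Solothurn, "a 1:1 randomisation ratio was used in the initial study phase, and then changed to 1:2", giving an average of 1:1.6. Patients of trained GPs were randomised individually, with households kept together. No stratification by GP or phase is described.

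**The concern.** When the allocation probability changes during enrolment, randomisation balances the arms within each phase but not across the pooled sample. The pooled contrast is then unbiased only if outcomes do not differ by phase.

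The article offers reasons why they might differ. Final inclusion began in November 2000 and ended in Solothurn in February 2002, so one-year follow-up would fall in different seasons. Trained GPs, who also treated the controls, had follow-up sessions every two to three months, so early and late entrants may have met them at different stages of training. The mix of GPs may also have shifted. At stake is a systematic arm difference in Solothurn that none of the described randomised comparisons would remove.

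A lesser point concerns all sites. GP is known before randomisation and probably predicts outcomes such as blood pressure, cholesterol and glucose checks, the two vaccinations and faecal occult blood testing. Leaving it out puts between-GP variation into the error.

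**Working it through.** **1. The plan's own figures.** The sample-size section sets a test "at a two-sided significance level of 0.05 and with a power of 80" percent, "a postulated 30% difference in positive health risk behaviour or preventative care use", and "a prevalence of positive behaviour or preventative care use among controls of 20% was assumed". Read as a relative difference, this is 20% versus 26%, a 6-point target. The continuity-corrected two-proportion formula gives 805 per group. Allowing for 20% drop-out, 805/0.80 is about 1007, against the stated 1000. At 1:2 it gives 745 and 1490, against the stated 763 and 1525. Both agree within 3%, which supports the 6-point reading. The average ratio also reproduces: 1410/874 = 1.61.

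**2. Size of the Solothurn phases.** Let N1 be the number randomised at 1:1, out of 874 + 1410 = 2284.

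- Intervention arm: N1/2 + (2284 − N1)/3 = 874
- N1/6 = 874 − 761.33 = 112.67, so N1 = 676, and 1608 entered at 1:2
- Share of each arm from the 1:1 phase: 338/874 = 38.7% of intervention, 338/1410 = 24.0% of controls
- Gap: 14.7 points

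These are expected-value solutions. Under simple randomisation of persons (an assumption), the intervention count has SD √(676 × 1/4 + 1608 × 2/9) ≈ 23, so N1 is uncertain by about 6 × 23 = 138. N1 = 538 gives 269/851 − 269/1433 = 12.8 points. N1 = 814 gives 407/897 − 407/1387 = 16.0 points. The gap is therefore not sensitive to this.

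**3. Bias.** Bias = 0.147 × outcome difference between phases. The phase difference is assumed, because the article gives none. For type I error I take a 20% rate and 80% retention, so SE = √(0.16 × (1/699.2 + 1/1128)) = 1.93 points.

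| Assumed phase difference | Bias | Share of 6-point target | Type I error at nominal 5% |
|---|---|---|---|
| 5 points | 0.7 | 12% | 6.7% |
| 10 points | 1.5 | 25% | 11.9% |

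**4. If GP mix alone drives the difference.** I simulated no true effect with 22 GPs (assumed), a 20% or 50% outcome rate and 1500 runs per setting. The Monte Carlo SE is √(0.05 × 0.95/1500) ≈ 0.6 points.

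- GPs entering fully in stages, unadjusted test: about 6% type I error at a between-GP intraclass correlation (ICC) of 0.05, and 7% to 8% at 0.10. The first is barely distinguishable from 5%.
- Same setting with a GP term or a phase term: near 5%.
- GPs spread evenly over both phases, unadjusted test: near 5%.

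**5. Precision from a GP term.** The ratio of unadjusted to adjusted variance is roughly 1/(1 − ICC): 1.01, 1.05 and 1.11 for assumed ICCs of 0.01, 0.05 and 0.10. Solothurn power for 20% versus 26% at 80% retention, without continuity correction, is 84.5% unadjusted and 84.8%, 86.2% and 88.0% with GP. This is a linear-model approximation for binary outcomes.

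**The case against.** The strongest reply has four parts.

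- **The model already respects the unit randomised.** Household is the unit, and it is in the model. At a constant ratio nothing more is needed for validity. This stands for London and Hamburg: a reader might infer that omitting GP biases those comparisons or inflates their type I error, but with randomisation among the trained GPs' patients at one ratio it does neither.
- **Nothing says GPs entered Solothurn in stages.** All 33 GPs agreed, and practices listed patients and then invited everyone left on the list. This stands. It would go too far to say GP mix differs between arms by design. Only the imbalance in phase follows from the design; whether GP mix, season or training stage follows phase is unknown.
- **A 10-point phase gap is large if GP mix is the only source.** With 22 GPs split 6.5 early and 15.5 late, and a 20% rate, the between-GP SD is 8.9 to 15.5 points for ICC 0.05 to 0.15. Multiplying by √(1/6.5 + 1/15.5) = 0.467 gives an SD for the early-late difference of 4.2 to 7.2 points, so a one-SD difference means 0.6 to 1.1 points of bias. This is fair, though season and training stage could add to it.
- **The precision gain is narrow.** It concerns mainly 6 of the 16 one-year outcomes and rests on assumed ICCs. In London only practice (three units) would be used, so the between-GP figure does not carry over. All of this stands.

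A reader might also take the Solothurn difference in fair or poor health (19.9% versus 24.8%, p = 0.007 by chi-square) as proof of a phase effect. It is not. Phase imbalance alone would need a phase difference of about 4.8/0.147 = 33 points, which with an overall rate of 523/2284 = 22.9% would put the early phase at about zero. London, at a constant 1:1, shows a comparable imbalance in doctor visits (19.0% versus 24.3%, p = 0.001).

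The article refers to an a priori analytic plan that is not shown, and covariate detail could sit there. But the article itself states both the main model and the adjusted repeat, and neither contains phase.

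**Conclusion.** The point holds for Solothurn. About 39% of the intervention arm but 24% of controls come from the 1:1 phase, and no randomised comparison in the article accounts for it. The imbalance follows from the reported arm sizes and stated ratios; the bias does not. Bias requires outcomes to differ between phases, on which the article is silent. With an assumed difference of 5 to 10 points it is about 0.7 to 1.5 points, or 12% to 25% of the 6-point target, in a direction that cannot be predicted.

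The GP or practice covariate is a separate efficiency suggestion. Without it the variance is about 1% to 11% larger for assumed between-GP ICCs of 0.01 to 0.10, mainly for the six GP-delivered care items, and Solothurn power stays above 80% on the plan's own assumptions. It is not a validity defect at a constant ratio. Correcting the Solothurn analysis is worthwhile because it is cheap and guards against a known feature of the design.

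**What to change.** In Solothurn, add allocation phase (1:1 versus 1:2) as a covariate in the main GEE model, or stratify the comparison by phase, keeping household as the cluster. Do the same for the two-year analysis, which uses the same randomised arms. A GP term alone is not a substitute, because it does not remove change over time within a GP. Nor is collapsing to practice circle, which leaves only two units.

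As an additional precision measure, add GP (Hamburg, Solothurn) or practice (London) as a covariate, merging small GPs where outcomes are sparse. Report the household-only model as a sensitivity analysis.

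The cost is analysis wording and some parameters. Phase should be recoverable from the study centre's allocation records, and GP from the practice lists. Phase needs one term. Practice needs 2 in London, and GP needs 13 in Hamburg (14 trained GPs) and about 20 in Solothurn. Odds ratios become conditional on phase and on GP or practice, which should be stated when they are reported.
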